#### Contamination

Residents in the Facility Model clusters could be exposed to the community intervention (e.g. flyers, community events). Such contamination could potentially bias the trial results towards the null, reducing the estimated effect of the community intervention. We will mitigate the effect of potential contamination through our design (limiting the geographical contiguity of clusters), by estimating potential contamination, and through statistical analysis. We will estimate contamination at baseline by asking those who are screened whether they have been exposed to any of the components of the community intervention (e.g. attended awareness events, saw flyers). These data will be used to conduct sensitivity analysis estimating the contamination range and the actual treatment effect.

### Participant timeline {13} (Table 4)

**Table 4 Tab4:**
[figure not shown]
Schedule of enrolment, interventions, and assessments

Participants will be identified and recruited by the trained and supervised case managers at the health centres. Health centre attenders meeting the eligibility criteria will be screened using the PHQ-9 questionnaire [29], a nine-item questionnaire that has been validated and extensively used in the study setting [15, 30]. Participants who score > 4 (mild depression and above) will contribute to the contact coverage outcome.

Due to the limited caseload capacity of the counsellors, we will prioritise HAP for the most severely unwell, who have also been shown to derive the greatest benefit from such interventions [31]. This means that only those who score ≥ 15 (moderately severe to severe depression) will be eligible to receive the HAP intervention and will contribute to the effectiveness coverage outcome. After consent has been obtained from those eligible for the effectiveness coverage component, the case manager will collect the data on the following potential effect-moderators: age, gender, marital status, education and employment status; and other outcomes: WHODAS 2.0, MSPSS, and PAAS. All assessments will be audio-taped (with consent), and the tapes will be randomly selected for review by the supervisor for quality assurance. The outcomes will be measured at 3 and 6 months post recruitment. The qualitative data with trial participants will be collected after the 6-months outcome evaluation. The process data will be collected at various timepoints during the implementation as outlined in Table 3.

### Sample size {14}

#### Contact coverage outcome

We will screen for 5 days a week for 12 months (52 weeks) in all 30 health centres. Based on screening numbers over the first two months of the trial (average of 6624 per month), we will be able to screen 79,488 over 12 months. Based on the screening data from the first 2 months of the IMPRESS trial, the prevalence of depression (PHQ-9 score > 4) amongst those screened at the health centres is 14%. Assuming this prevalence in health centres in the Community Model, this sample size provides 86% power to detect a difference with a prevalence of 11% in those screened at the health centres in the Facility Model at the 5% significance level, assuming a coefficient of variation of 0.2 as below.

#### Effectiveness coverage outcome

Twenty-one participants with a PHQ-9 score ≥ 15 will be recruited from each of the 28 clusters (*N* = 588). Allowing for 20% of participants to be either not traceable by the outcome assessors or to not consent to participate at follow-up, we expect 17 participants from each cluster to complete the outcome evaluation at the three-month endpoint. This gives a sample size of 476 in which to assess our effectiveness coverage outcome at three months. This sample size provides 80% power to detect an effect size (standardised mean difference (SMD)) of 0.4 at the 5% significance level, assuming a coefficient of variation between clusters of 0.2. The assumptions underlying this calculation are based on the HAP trial for the effect size (i.e. a difference between the mean PHQ-9 scores of 11.9 [SD = 7.0] in the control arm and 8.9 [SD = 7.2] in the intervention arm) and the MANAS trial for the coefficient of variation (this trial tested a psychosocial intervention for common mental disorders in the same setting [32, 33]).

### Recruitment {15}

We will continue screening in the 30 health centres in Goa, India, until we achieve the sample size mentioned above. Based on our experience of implementing trials in this setting, we expect to achieve the planned sample size over 12 months of screening and recruitment.

## Assignment of interventions: allocation

### Sequence generation {16a}

The allocation sequence was generated through restricted randomisation using the following parameters: (a) type of health centre (PHC, CHC, SDH) associated with the cluster; (b) availability of DMHP services in the health centre; and (c) population size of the cluster. A randomly selected seed number was used to enable the randomisation procedure to be reproduced. The randomisation was done before the start of the trial as both the embedding of the trial and other implementation processes (e.g. training of community intervention delivery agents) had to be initiated in advance of recruitment of the first participant.

### Concealment mechanism {16b}

An independent statistician conducted the randomisation procedure and communicated the allocation of clusters only to the data manager and community intervention coordinator to initiate relevant procedures in the Community Model clusters (e.g. identification of *Sangathis*). The coordinator will share the information only with those members of the team who would naturally remain unblinded because of the nature of their role (e.g. *Sangathi* facilitators).

### Implementation {16c}

The enrolment of participants will be done by case managers. All consenting participants in the Facility Model will receive HAP, and those in the Community Model will receive support from the *Sangathi* in addition to the HAP.

## Assignment of interventions: blinding

### Who will be blinded {17a}

Throughout the trial, the lead principal investigators and co-investigators, programme director, research coordinator, outcome team coordinator, outcome assessors, and trial statistician will be blinded to arm allocation. Given the nature of the interventions and the roles, the following will be unblinded: participants, counsellors, *Sangathis*, case managers, HAP facilitators, *Sangathi* facilitators, data operators and data manager, and clinical coordinators.

Blinding will be maximised by:Allocating unique participant IDs which have no association with the cluster and arm identityAllocating a random alphabet as an ID to clustersEnsuring that the outcome assessors’ team is separate from the rest of the team, comes to office only on weekends and is not privy to the randomisation allocationEmphasising to assessors that all patients are receiving an intervention (not specifying whether this is only HAP or HAP plus the community intervention) and that there is genuine equipoise about which is betterAdministering the PHQ-9 (the primary outcome) prior to all other outcome and qualitative assessmentsEnsuring that process and qualitative research evaluations are carried out independent of the quantitative evaluations; the qualitative research will be carried out by a separate team only after the quantitative evaluation is complete

### Procedure for unblinding if needed {17b}

No procedure for unblinding is planned for this trial.

## Data collection and management

### Plans for assessment and collection of outcomes {18a}

The individual level effectiveness outcomes will be assessed at the participants’ homes, any other convenient location, or over the phone by a team of researchers independent of the intervention team and blind to the allocation status of the participant. The primary endpoint assessment will occur within 4 weeks of the 3-month endline date and similarly for the 6-month endline. The qualitative data will be collected by a team of researchers which is independent from the outcome evaluation team and treatment providers.

### Plans to promote participant retention and complete follow-up {18b}

All participants will be informed about the importance of timely follow-up and of their contribution during the consenting process. For each of the two follow-ups, there will be a 4-week window to maximise the chances of completing the outcome assessments. As there is a possibility that some participants are unable to complete the assessments within this window, we will not reject any outcome assessments done outside this window, and we will conduct a sensitivity analysis after excluding any such assessments. Whenever we have issues with contacting the participant, we will make three attempts using different modalities (e.g. phone call, home visit) at different times of the day on different days of the week to maximise the chances of completing the assessment.

### Data management {19}

All screening, baseline, and outcome data will be collected and managed using REDCap, a secure, web-based software platform for data collection in research studies. All members of the team involved in data collection are trained about the study procedures to ensure consistent and reliable data collection. All the digital data (including audio-recordings) will be saved on a secure institutional server and backed up to a secure cloud server on a weekly basis. Access to pre-locked data will be password-protected at multiple levels, and no member of the trial team apart from the data team and statistician will have access to these passwords. The PIs will have access to all the anonymised trial data and will decide about the access privileges to the database. The data manager and the data team working under her supervision will be responsible for the following activities: (1) development of the data capture tools in REDCap, (2) data monitoring and quality control, and (3) data processing. The data team will prepare regular and blinded reports for monitoring of progress toward trial milestones. While the REDCap data entry system reduces data errors (for example, by not accepting out-of-range values), the data team will also conduct manual checks for the accuracy of the data. This will include checking for duplicate records, illogical entries, outlier values, and out of range values. As people are now recognisable by their voices, all audio recordings of interviews and counselling sessions will be deleted after transcription and analysis of the data. All paper data, including the signed consent forms, will be converted into digital files, and saved on the secure institutional server.

### Confidentiality {27}

All research staff will be trained in Good Clinical Practice guidance. All participant-identifying information on paper (e.g. signed consent forms) will be kept in locked cabinets accessible only to the data team. All electronic data will be password protected. The data obtained during the trial will be used only for the purpose for which the participant has consented. Each study participant will receive a unique identification number to which all their trial data will be linked. Audio files of recruitment, follow-up, and qualitative interviews will also be renamed using the corresponding participant identification number. The file that links participant names with the participant identification number will be kept in a single locked cabinet, accessible only to the data manager. Finally, all data will be reported only in an aggregate form.

### Plans for collection, laboratory evaluation, and storage of biological specimens for genetic or molecular analysis in this trial/future use {33}

This is not applicable as this trial does not involve collection of any biological specimens for genetic or molecular analysis.

## Statistical methods

### Statistical methods for primary and secondary outcomes {20a}

A detailed analysis plan will be agreed with the data safety and monitoring board towards the end of the trial and before any analysis is undertaken. Findings will be reported as per the CONSORT guidelines for CRTs. Baseline comparability will be assessed for participants who could and could not complete outcome assessments. Comparability of the two intervention arms will be assessed for potential confounding factors such as age, gender, education, and severity of depression at baseline.

#### Contact coverage

The primary analyses will compare the proportion of individuals identified with depression through screening in the health centres. Logistic regression will be used to compare the number of individuals between arms, allowing for within-facility clustering. We will also do a sensitivity analysis to examine the contact coverage for moderate depression and above (i.e. PHQ9 ≥ 9).

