### Eligibility criteria {10}

#### Trial clusters

Our a priori definition of the unit of randomisation was a cluster of villages and the health centre where the residents of those villages seek healthcare. We then used the Geographic Information System (GIS) [13] tool to assess the internal validity of our definition by mapping villages to the health centres in which their residents access healthcare. To reduce the risk of contamination between the two arms, a village is included in a particular cluster if (a) 75% of the healthcare-seeking population from that village accesses services at the health centre associated with that cluster, and (b) it has contiguous borders with other villages in the cluster.

We will measure contact coverage in all the 30 available health centres. However, for the effectiveness coverage we excluded two PHCs as no villages met both the aforementioned criteria with regard to those health centres. This was because the people from the villages surrounding these two PHCs access services from a better resourced SDH which is in close proximity. Thus, for the effectiveness coverage outcome, we randomised 28 clusters.

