#### Contact coverage (primary outcome)

The contact coverage outcome (PHQ-9 score > 4) will be documented directly through screening in the health centres. After confirming the village of residence of the screened individual, the contact coverage outcome will be allocated to the arm to which their village belongs, regardless of the health centre in which they screen positive.

The contact coverage population level outcome data will be collected through the period of the trial at all thirty health centres, i.e. even at the two health centres which will not be randomised. This is because, while these two health centres do not have discrete village clusters associated with them (as described earlier), individuals with depression from other randomised village clusters could potentially access depression care in these health centres and hence will contribute to the contact coverage outcome.

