#### Effectiveness coverage

The primary analyses will be intention-to-treat. Linear regression GEE will be used to compare mean PHQ-9 scores by arms, adjusting for within-facility clustering, baseline severity of depression and any confounding factors for which there is substantial imbalance between the arms at baseline. We will present an estimate of the effect size as an adjusted SMD and 95% confidence intervals and the intra-cluster correlation. For binary outcomes, the effect will be measured by the risk ratio (RR) and 95% confidence intervals using logistic regression models adjusted for within-facility clustering. Predefined effect-modification analyses will include adjustment for age, gender, marital status, education, employment status, and baseline PHQ-9 score. Finally, we will consider a sensitivity analysis to investigate the effect of missing data by using multiple imputation. We will not conduct an interim analysis as we do not anticipate any safety concerns related to the interventions.

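### The contact-coverage analysis allows only for clustering by facility, although arm is set by the randomised village cluster of residence; with cross-attendance this can understate the standard error.

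*Protocol article*

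**What the plan says.** All references are to the protocol article.

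- **Unit of randomisation** (section Trial clusters, under the eligibility heading): "Our a priori definition of the unit of randomisation was a cluster of villages and the health centre where the residents of those villages seek" (last word of the sentence cut). The unit thus joins villages and a centre. The section also says: "Thus, for the effectiveness coverage outcome, we randomised 28 clusters".
- **Where the outcome is measured** (same section): "We will measure contact coverage in all the 30 available health centres". Two of these have no village cluster of their own. The reason given for including them (Outcomes, Contact coverage) is that "individuals with depression from other randomised village clusters could potentially access depression care in these health centres".
- **How arm is assigned** (Outcomes, Contact coverage): "the contact coverage outcome will be allocated to the arm to which their village belongs, regardless of the health centre in which they screen positive".
- **How tightly villages are tied to a centre** (Trial clusters): a village joins a cluster if "75% of the healthcare-seeking population from that village accesses services at the health centre associated with that cluster" and it borders other villages of the cluster.
- **Analysis** (Statistical methods, Contact coverage): "Logistic regression will be used to compare the number of individuals between arms, allowing for within-facility clustering". No other clustering level is named, and neither is the method (GEE, random effect or robust variance) for this outcome.
- **Second primary outcome** (Statistical methods, Effectiveness coverage): "Linear regression GEE will be used to compare mean PHQ-9 scores by arms, adjusting for within-facility clustering".

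**The concern.** In a cluster-randomised trial the variance has to reflect the unit that carries the allocation. For contact coverage that unit is the randomised cluster of residence, because the outcome follows the person's village into the arm. The analysis groups people by screening facility instead. The two groupings agree for anyone screened at the linked centre and differ for everyone else.

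Cross-attendance has two effects. Residents of one randomised cluster appear in several facilities, and the analysis counts these as independent although they share a cluster effect and one allocation. A facility can also contain both arms, so that a facility-level working correlation treats part of the arm contrast as a within-facility comparison, which looks more precise than it is. The two centres without a cluster show this most clearly: eligibility is limited to residents of trial clusters, so everyone counted there belongs to a cluster linked to another centre.

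At stake is whether the interval and the 5% significance level hold for one of the two primary outcomes.

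**Working it through.** **1. Inputs from the protocol article.** 79,488 screened, 14% against 11%, coefficient of variation k = 0.2, 5% significance, 86% power (Sample size, Contact coverage outcome); equal allocation of clusters (Trial design); 28 randomised clusters and 30 centres (Trial clusters).

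**2. The stated power.** The usual unmatched cluster formula is

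power = Φ( √{ c′(p₁ − p₀)² / [ (p₁(1 − p₁) + p₀(1 − p₀))/m + k²(p₁² + p₀²) ] } − 1.96 ),

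with m = 79,488/(2c), c clusters per arm, and c′ = c − 1 or c.

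For c = 14, m = 2,839:
- sampling term: (0.1204 + 0.0979)/2,839 = 0.000077
- between-cluster term: 0.04 × (0.0196 + 0.0121) = 0.001268
- sum: 0.001345

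| Clusters per arm | c′ | Power |
|---|---|---|
| 14 | 14 | Φ(3.061 − 1.96) = 86.4% |
| 15 | 14 | Φ(3.055 − 1.96) = 86.3% |
| 14 | 13 | Φ(2.949 − 1.96) = 83.9% |

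The 86% is reproduced in two ways, one with 28 units and one with 30, so it is not shown to be wrong. The useful by-product is that the between-cluster term is 0.001268/0.001345 = 94% of the variance. The level at which clustering is modelled therefore determines almost all of the standard error.

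**3. A hand approximation.** Assume that all between-cluster variation is at residence level and that a share x of each cluster is screened elsewhere, spread thinly. A facility-robust variance under working independence keeps the covariance within the main centre, about (1 − x)² of the true cluster variance, and loses the rest. The standard error is then about (1 − x) of what it should be, and the true level of a nominal 5% test is 2[1 − Φ(1.96(1 − x))]:
- x = 0.05: ratio 0.95, level 6.3%
- x = 0.15: ratio 0.85, level 9.6%
- x = 0.25: ratio 0.75, level 14.2%

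**4. Simulation under the null.** 700 trials per scenario, prevalence 12.5%, k = 0.2, 28 randomised clusters, up to 30 facilities. The share screened elsewhere (5% to 25%) and the split of variation between residence and facility are assumptions. Entries for facility clustering are the ratio of mean to true standard error, then type I error.

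| Variation at | Independence, robust | Exchangeable, robust | Exchangeable, model-based |
|---|---|---|---|
| Residence only | 0.94 to 0.76; 6–14% | 0.75 to 0.61; 14–23% | 0.62 to 0.33; 19–49% |
| Half and half | 0.98 to 0.87; 5–10% | 0.80 to 0.67; 11–19% | 0.76 to 0.44; 13–36% |
| Facility only | 0.96 to 1.03; 4–5% | 0.90 to 1.05; 3–8% | 0.95 to 1.05; 3–5% |

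Clustering on the residence cluster kept the ratio at 0.93 to 1.03 and type I error at 4.3% to 7.9% in all scenarios with cross-attendance. With 700 runs, a true 5% has a Monte Carlo standard error of √(0.05 × 0.95/700) = 0.8 points, so differences of one or two points mean little. The first cell agrees with step 3.

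**5. Baseline.** With no cross-attendance the two groupings coincide and the unit makes no difference. A separate simulation of 4,000 null trials per scenario, with residence-level variation only and facility clustering, rejected in 6.8% with no cross-attendance, 10.3% at 10% and 15.2% at 25%. The first 1.8 points above 5% therefore come from the small number of clusters, not from the choice of unit.

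**The case against.** The best defence is that the health centre is part of the randomised unit. Twenty-eight of the 30 facilities are each linked to one randomised cluster, most people should attend their own centre, and within-facility may be shorthand for within-cluster. The Effectiveness coverage paragraph does report an intra-cluster correlation from a facility-adjusted model. This stands as a reason to expect a modest problem. It does not remove the problem, because the outcome definition separates arm from screening centre and adds two centres that have no cluster.

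Further points that stand:
- The 25% is a ceiling implied by the village-inclusion rule, not an expected rate. No cross-attendance figure is given, and movement between clusters of the same arm does not mix arms. The Contamination section says that contiguity of clusters is limited by design. People around the two unlinked centres are said to use a nearby sub-district hospital, which gives no sign of a large inflow there.
- Screening is done by case managers based in the health centres, so some variation may truly be at facility level, where facility clustering is close to valid. On the other side, awareness events and home visits take place in the villages, so residence-level variation is also plausible.

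A reader might infer that the standard errors are certainly too small, or that every facility holds both arms. The document supports neither. A reader might also extend the error to the PHQ-9 outcome because the same wording is used there. The rule assigning arm by residence is stated for contact coverage only, and the PHQ-9 sample is 21 participants from each of the 28 clusters, so no mismatch is shown. Finally, the absence of a stated small-sample correction is not a defect here: a detailed analysis plan is to be agreed before analysis.

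**Conclusion.** The point holds for contact coverage, conditionally. The protocol names a clustering unit that conflicts with its own allocation rule. This is not a detail left open: an analysis plan that followed the sentence as written would inherit the conflict.

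The size is uncertain. With 5% to 25% screened elsewhere and all variation at residence level, type I error is about 6% to 14% under the mildest implementation, and more with an exchangeable correlation. With negligible cross-attendance or purely facility-level variation there is little or no inflation. The range rests on assumed cross-attendance, an assumed variance split and a method that the article does not name. No error is shown in the PHQ-9 analysis or in the stated 86% power.

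**What to change.** In Statistical methods, Contact coverage, replace within-facility clustering by clustering on the 28 randomised village clusters of residence. Include screening facility as an additional crossed level, or use it in a sensitivity analysis. Residents screened at any of the 30 centres, including the two without a cluster, should enter under their cluster of residence.

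In Effectiveness coverage, name the randomised cluster instead of the facility, for consistency only. When the detailed analysis plan is written, a small-sample variance correction with 28 clusters is a sensible addition.

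Village of residence is already confirmed at screening, so no new data are needed. The cost is wording and possibly slightly wider intervals. Tabulating cluster of residence against screening centre, without outcome data, would show how much cross-attendance there is before analysis.
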